### 2.7. Secondary Outcomes

#### 2.7.1. Physical Fitness, Muscle Endurance, Muscle Strength, Balance

A trained researcher will use the ID-fitscan to assess physical fitness. The ID-fitscan is a standardised set of performance tests that assesses muscle endurance (30 s chair stand and the five times chair stand), muscle strength (grip strength by hand-held dynamometry), and balance (four balance stances and comfortable walking speed). The set has been found feasible and reliable for adults with ID [36].

For the 30 s chair stand, participants are instructed to stand up and sit down as often as possible, without using their hands. We will record the number of complete stances performed in 30 s. For the five times chair stand, participants are instructed to stand up and sit down five times as fast as possible, without using their hands. We will record the time needed to complete five stances. For both tests, the participant starts sitting in the chair with the feet on the floor and the knees in a 90° angle.

We will use the Jamar dynamometer (Hydraulic, JAMAR, Sammons Preston Rolyan, Nottinghamshire, UK) to measure grip strength. Grip strength is tested in a seated position with the shoulder in 0° flexion and the elbow in 90° flexion. The participant is asked to squeeze the dynamometer with maximum force three times, with one minute rest in between. Both hands will be tested. The maximum produced force of the six attempts (kg) is the final test score.

Static balance will be measured with four stances that increase in difficulty: side-by-side stand, semi-tandem stand, tandem stand, and single leg stand. The participant must try to maintain each stand independently for 10 s for both sides, with a maximum of five attempts. If successful, the participant continues to the next stand. We will record the time for each completed stance and use the scores for side-by-side stand, semi-tandem stand, and tandem stand to categorise static balance from 0 (worse) to 4 (best) [37]. Dynamic balance will be measured as comfortable gait speed on an 11 m walkway. The participant will start from stance and accelerate to comfortable gait speed in the first 3 m of the walkway. When crossing the 3 m mark, a stopwatch is put in action and gait speed will be measured over the following 5 m. At the 8 m mark timing will be ended, and the participant will decelerate to standing still over the last 3 m of the walk. The test will be repeated three times. The average time of the three trials (seconds) will be converted to gait speed (m/s).

#### 2.7.2. Sarcopenia, Body Composition

We will use bioelectrical impedance analysis (Tanita Body Composition Analyzer MC-780, Tanita, Tokyo, Japan) to measure body mass (kg), fat mass (kg and %), and muscle mass (kg and %). The Tanita MC-780 estimates muscle mass based on whole body conductivity and uses a conversion equation that is calibrated with Dual-energy X-ray absorptiometry as a reference [38]. Muscle mass will also be measured by calf circumference. A trained researcher will use a measuring tape (Seca 200, Seca, Hamburg, Germany). Calf circumference will be measured twice at the widest point of the calf. If both measurements are within 1cm of one another, we will calculate an average score (cm). If the difference between the measurements exceeds 1cm, the two measurements will be repeated.

Table 3 presents the cut-off values that we will use to classify participants as being sarcopenic [17]. We will classify participants that score under the cut-off values for muscle endurance, muscle strength and muscle mass as sarcopenic. If participants also score under the cut-off value for comfortable gait speed (≤0.8 m/s), they will be classified as severe sarcopenic [17].

#### 2.7.3. Physical Activity

To assess the physical activity levels, we will use the International Physical Activity Questionnaire (IPAQ) [39]. The IPAQ assesses daily physical activity over the last seven days. The IPAQ consists of 27 items that are divided into five domains of physical activity: job-related, transportation, housework, leisure time, and sitting. For each domain, scores are provided for walking, moderate-intensity activities, and vigorous-intensity activities. Scores will be reported as the estimation of metabolic equivalent-minutes per week (MET-minutes/week) [40]. The IPAQ has been found reliable and valid in the general population [39].

#### 2.7.4. Activities of Daily Living

We will use the Barthel Index [41] to assess the ability to perform basic activities of daily living. The Barthel Index consists of ten items (bowel control, bladder control, grooming, toilet use, feeding, transfer, walking, dressing, climbing stairs, and bathing) with item scoring categories ranging from two to four categories. The total score ranges from 0 (completely dependent) to 20 (completely independent) [42]. The Barthel Index has good psychometric properties in the general population [42].

To assess the ability to perform instrumental activities of daily living (IADL), we will use an adapted version of the Lawton IADL scale [43]. We expect that adding and rephrasing some items for preparing food, housekeeping, and doing laundry, will increase the responsiveness of the scale. In a previous study we found this version to be applicable in older adults with ID [44]. The items were derived from the Groningen Activity Restriction Scale (GARS) [45]. All items will be scored on a 4-point rating scale ranging from 0 (not at all, with complete help) to 3 (fully independent, without any difficulty). All items scores will be summed. A detailed description of the items and scoring is presented in Table 4. We will administer the Barthel Index and the adapted version of the Lawton IADL scale as an informant-based questionnaire, completed by the professional caregiver of the participant.

#### 2.7.5. Falls

We defined a fall as an event that results in a person coming to rest inadvertently on the ground, floor, or other lower level [46]. We will use a fall calendar during the baseline period and the 12-week follow-up period. Falls are logged daily by the participant or the involved professional caregiver by putting a green sticker (no fall) or a red sticker (fall) on the calendar. If a participant falls multiple times during the day, the number of falls will be written down. The professional caregiver will check the calendar for completeness. For each period, we will classify participants as a non-faller or a faller (≥1 fall).

#### 2.7.6. Challenging Behaviour

We will evaluate challenging behaviour with the Aberrant Behaviour Checklist (ABC) [47]. The ABC consists of 58 items that are divided into five subscales: irritability, lethargy, stereotypic behaviour, hyperactivity, and inappropriate speech. Items are scored on a four-point scale ranging from 0 (not a problem) to 3 (severe problem) by the professional caregiver of the participant. The summed score of each subscale will be recorded separately [47]. The ABC is a reliable and valid instrument in adults with ID [48].

### 2.8. Adverse Events

Adverse events are defined as any undesirable experience occurring to a participant during the study. It does not matter if the event is related or unrelated to the experimental intervention. Adverse events can be reported spontaneously by the participant, trainer, or professional caregiver. All adverse events will be recorded by the researcher.

### 2.9. Participant Characteristics

Age, sex, ethnicity, level of ID, aetiology of ID, family history of CVRF (yes/no), kidney disease (yes/no), and medication use related to CVRF, are collected from medical records. The level of ID will be categorised as mild (IQ = 50–69) or moderate (IQ = 35–49). Professional caregivers will provide information about residential setting, sport activities, smoking, and alcohol use.

### 2.10. Procedures

Figure 1 shows a schematic representation of the study procedures. Participant characteristics will be collected at T0. During the 12-week baseline period, measurements for the primary and secondary outcomes will take place at six-week intervals (T0, T1, and T2). A minimum of three measurements is needed to establish a valid baseline and to filter out the natural variability that may exist in these parameters without applying any intervention [49]. We will record changes in sport activities and medication use related to CVRF. The falls will be tracked continuously throughout the 12-week baseline period.

After the baseline period, the intervention period starts for a duration of 24 weeks. We will record changes in sport activities and medication use related to CVRF. At the end of the intervention period all measurements for the primary and secondary outcomes will be repeated (T3).

The follow-up period will last 12 weeks. Directly post-intervention, we will ask all participants to fill out a questionnaire about their experiences with the PRET programme. We plan interviews with participants and their trainers who want to continue the PRET programme and evaluate facilitators and barriers for successful exercise in their daily life. At the end of the follow-up period all measurements for the primary and secondary outcomes will be repeated (T4). Falls will be tracked continuously throughout the follow-up period. Participants who drop out prematurely from the intervention, will be invited for the measurements at T3 and T4.

### 2.11. Statistical Analysis Plan

#### 2.11.1. Baseline Characteristics

Descriptive statistics will be used to present group characteristics for age, sex, ethnicity, level and aetiology of ID, family history of CVRF, kidney disease, use of medication, and primary and secondary outcomes at T0. We will use the mean and standard deviation (SD) to present normally distributed data, the median and interquartile range for non-normally distributed data, and the number and percentages for categorical variables.

#### 2.11.2. Effect of PRET Programme (Post-Intervention)

We will use two-level hierarchical linear and logistic regression models to investigate the effect of the PRET programme at the end of the intervention period (T3). The first level consists of the repeated measurements nested within a participant; the second level consists of the clustering of participants by the trainer delivering the PRET programme. We will use the likelihood ratio test (correcting for the boundary) to assess the necessity for random coefficients in the regression model. Statistical analyses will be performed with R-statistics (R Foundation for Statistical Computing, Vienna, Austria) and we will use the package Linear and Nonlinear Mixed Effects Models (nmle) [50]. A two-tailed significance level of 0.05 will be used for all tests.

The variables for the PRET programme will be coded as 0 (baseline period at T0, T1, and T2) or 1 (intervention period T3). To check the assumption of stable baseline measurements, we will investigate the effect of time on each outcome variable assessed during the baseline period. Time varying variables (changes in sport activities and medication use related to CVRF) will be included as covariates in all models.

We will use the data from all participants who started the study. We will also analyse the effect of the intervention for participants who completed the intervention as planned.

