### 2.12. Sample Size Calculation

We calculated the sample size for the outcome HbA1c using simulated data and repeated the simulation a 1000-times in a hierarchical way. To determine the effect of the trainers we used the outcome of our pilot study [25] where we found a variation of 30% for the clustering of participants by the trainer who delivered the PRET programme. The type 1 error (alpha) was set at 0.05 and power was set at 80%. We used an effect size (mean change in %HbA1c = −0.55, SD = 0.47) derived from a study that examined the effect of high intensity resistance training in adults with diabetes mellitus type 2 [10]. This resulted in a sample of 35 participants needed for this study. In our pilot study, 58% of the participants completed the PRET programme successfully at intended intensity [25]. Therefore, we inflate the number of participants by 42% and aim to enrol 61 participants in this study.

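### If the PRET effect differs between trainers and is tested with within-participant degrees of freedom, the 5% test for linear outcomes is too liberal when trainers are few

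*Protocol article*

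**What the plan says.** Section 2.11.2 specifies two-level linear and logistic models. Repeated measurements are nested in participants, and "the second level consists of the clustering of participants by the trainer delivering the PRET programme". PRET is coded 0 at T0, T1 and T2 and 1 at T3. A boundary-corrected likelihood ratio test decides whether random coefficients are needed. The analysis uses a mixed-effects package in R, and "A two-tailed significance level of 0.05 will be used for all tests". Changes in sport activity and in medication enter every model as covariates.

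Section 2.12 sizes the study on HbA1c, with a mean change of −0.55 and an SD of 0.47, by hierarchical simulation. For the trainers it relies on a pilot: "we found a variation of 30% for the clustering of participants by the trainer who delivered the PRET programme". The result is "This resulted in a sample of 35 participants needed for this study". Then "we inflate the number of participants by 42% and aim to enrol 61 participants in this study".

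Three things are not stated: how degrees of freedom are set for the PRET coefficient, how many trainers there are, and whether the 30% describes outcome level or response to PRET.

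**The concern.** Every participant contributes both baseline and post-intervention measurements, so PRET varies within participants. A mixed-model routine that assigns degrees of freedom by the innermost level at which a term varies would treat the PRET coefficient as estimated on nearly all the observations. That is correct if the effect is the same whoever delivers the training. If the effect differs by trainer, the information about its mean comes largely from the trainers. The appropriate reference distribution is then close to a t with (number of trainers − 1) degrees of freedom.

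With few trainers the two references differ a great deal. P-values would be too small and confidence intervals too narrow for the continuous primary outcomes (blood pressure, waist, lipids, glucose, HbA1c). This is a single-group study with several primary outcomes, each tested at 0.05, so little else would catch a false positive. On the same reading, power depends mainly on the number of trainers and only weakly on the number of participants.

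**Working it through.** **1. The plan's own figures.** Enrolment reproduces: 35 / 0.58 = 60.3, rounded up to 61. The 35 cannot be reproduced from the stated inputs, because the number of trainers and the variance split are missing. With no clustering, the standardised change is 0.55 / 0.47 = 1.17. A paired t-test then needs 8 participants (power 81%), and 35 would give more than 99.9%.

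**2. Within-participant degrees of freedom.** With 61 participants, four visits, and three fixed effects (PRET and two covariates): 4 × 61 − 61 − 3 = 180. The two-sided 5% critical value is 1.973. That the test uses this number is an assumption about the named package's default.

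**3. Type I error if the effect varies by trainer.** Assumption: 30% of the variance of participant change lies between K trainers. In the limit where trainer variation dominates, the error is 2 × P(t with K − 1 df > 1.973). The simulated columns use a random-effects model for change fitted by REML, with a 30% share and 60 participants spread evenly over trainers.

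| Trainers K | Limit, 180 df | Simulated, 180 df | Simulated, K − 1 df | Simulated, 180 df, likelihood ratio test may drop the trainer effect |
|---|---|---|---|---|
| 3 | 18.7% | 17.3% | 2.9% | 21.2% |
| 4 | 14.3% | 13.5% | 4.1% | 16.6% |
| 5 | 12.0% | 11.5% | 4.5% | 14.0% |
| 6 | 10.6% | 10.3% | 4.6% | 12.4% |
| 10 | 8.0% | 7.8% | 4.8% | 9.5% |
| 20 | 6.3% | 6.3% | 5.0% | 7.6% |

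With a 10% share instead of 30%, the 180-df test runs at about 13%, 10%, 9%, 7% and 6% for 3, 4, 5, 10 and 20 trainers. The last column shows that letting the likelihood ratio test remove the trainer-varying effect makes the error larger.

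**4. Type I error if the 30% is a trainer intercept.** The intercept is present at T0–T2 and at T3, so it drops out of the contrast. Simulated error is 4.8% to 5.1% for 3, 6 and 10 trainers.

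**5. Power on the effect reading.** The standard error of the mean change is 0.47 × √(0.3/K + 0.7/N), and power comes from the noncentral t with K − 1 df. Example with K = 4 and N = 61: 0.3/4 + 0.7/61 = 0.0865, the standard error is 0.47 × 0.294 = 0.138, the noncentrality is 0.55 / 0.138 = 3.98, the critical value on 3 df is 3.18, and power is 75%.

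| Trainers K | N = 35 | N = 61 |
|---|---|---|
| 3 | 46% | 48% |
| 4 | 72% | 75% |
| 5 | 87% | 90% |
| 6 | 94% | 96% |

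Going from 35 to 61 participants adds at most about four points. With 4 trainers, even N = 400 gives 79.5%.

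**The case against.** The strongest objection is that the liberal error rate needs three conditions, none of which the article states.

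- **Degrees of freedom.** Section 2.11.2 names a package and a significance level but no df rule. The 180 is inferred. This stands, so a reader may not say that the plan will test PRET on 180 df, only that it may do so by default.
- **Meaning of the 30%.** Clustering of participants by trainer is ordinarily read as an intercept, and an intercept does no harm here. This also stands as a possibility. Against it, trainers deliver PRET only after T2, so their influence plausibly shows in the response to training, and section 2.12 introduces the 30% as a way to determine the effect of the trainers. Differences between care providers could still produce an intercept.
- **Number of trainers.** Three care providers and supervision at 1:1 or 1:2 are compatible with many trainers. At 20 the error is about 6%, which matters little.

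A reader might also infer that the step from 8 participants to 35 can come only from the trainer share, so that the 35 itself proves the effect reading. The documents do not support this. In the formula above, a normal test reaches 80% power at N = 29 with 2 trainers, 10 with 3 and 8 with 4. With K − 1 df, no N up to 2,000 reaches it with 2 or 3 trainers, while 5 trainers need 20 and 6 need 12. No trainer count tried returns 35. The nearest match, 2 trainers with a normal test and 81% power at N = 35, implies fewer trainers than care providers. The sponsor's simulation probably had a different structure.

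**Conclusion.** The point holds conditionally. If the PRET effect varies between trainers with a share of about 30%, and PRET is tested with within-participant degrees of freedom, the nominal 5% test for linear outcomes runs at about 17% with 3 trainers, 13.5% with 4, 10% with 6, 8% with 10 and 6% with 20. If the 30% is a trainer intercept only, the error stays at about 5% and no correction is needed.

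Two stronger conclusions are tempting and not supported. The first is that p-values for all linear primary outcomes are too favourable; that requires the effect reading, the package default and few trainers together. The second is that the stated 80% power is missed. On the effect reading with a trainer-level test it falls short only with about four trainers or fewer, and the article does not give the count. The omission of that count from 2.12 is in itself only missing detail.

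It is still worth acting on. The better method is specific and cheap, matters little if trainers are many, and prevents false-positive claims if they are few. The logistic models and the McNemar test for falls were not examined.

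**What to change.** In section 2.11.2, keep a trainer-varying PRET effect in the linear models whatever the likelihood ratio test shows. Test PRET, and form its confidence interval, with small-sample degrees of freedom that respect the trainer level (Satterthwaite or Kenward-Roger), in software that supports them.

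In section 2.12, rerun the existing simulation with this test, say whether the 30% is variation in level or in response, and report power by number of trainers. N does not need to change.

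The cost is a few sentences, a rerun and possibly different software. Intervals become wider if trainers are few. The test may also be somewhat conservative with very few trainers or little trainer variation. For orientation, the simple K − 1 df test ran at 2.9% with 3 trainers and a 30% share, and at 3.2% with 9 trainers, 36 participants and a 10% share.

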## 2. Material and Methods

### 2.1. Study Design

This study has a repeated time series design with one study group. The study period will last one year and is divided into a 12-week baseline period, a 24-week intervention period (PRET programme), and a 12-week follow-up period. We will use the baseline measurements for control comparisons.

This study follows the principles of the Declaration of Helsinki [27] and is in accordance with the Dutch Medical Research Involving Human Subjects Act. We obtained ethical approval from the Medical Ethical Committee of the Erasmus MC, University Medical Center Rotterdam in the Netherlands (MEC-2019-0544). The study is registered in the Netherlands Trial Register (NTR, NL8382). Written informed consent will be obtained from all participants or their legal representatives.

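### The PRET effect is T3 against the pooled baseline with no time term listed, so steady drift enters it at 2.5 times its baseline size, and the stability check would often miss it

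*Protocol article*

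**What the plan says.** The study has one group, and section 2.1 names its comparator: "We will use the baseline measurements for control comparisons". Section 2.10 sets the schedule: "measurements for the primary and secondary outcomes will take place at six-week intervals (T0, T1, and T2", and then "After the baseline period, the intervention period starts for a duration of 24 weeks", with T3 at its end.

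Section 2.11.2 fixes the effect variable: "The variables for the PRET programme will be coded as 0 (baseline period at T0, T1, and T2) or 1 (intervention period T3". The covariates it names are these: "Time varying variables (changes in sport activities and medication use related to CVRF) will be included as covariates in all models". Time appears only in a separate step: "To check the assumption of stable baseline measurements, we will investigate the effect of time on each outcome variable assessed during the baseline period". The level for that step follows from the general rule, "A two-tailed significance level of 0.05 will be used for all tests". The section gives no size of drift that would count as instability and no consequence for the PRET estimate if drift is found.

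**The concern.** The three baseline visits are the only control in this design. Pooling them into one level averages out random variation but does nothing about a trend. If an outcome was already moving before training began and kept moving, T3 minus the baseline mean contains that movement, and the model as listed assigns it to PRET.

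The stability check is the only stated protection, and it works over a much shorter span (12 weeks) than the contrast it is meant to protect. At stake is whether a significant PRET coefficient on a primary outcome can be read as an effect of training or only as a change over time.

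**Working it through.** **1. The plan's own figures.** Section 2.12 gives a mean change of −0.55 %HbA1c, SD 0.47, 35 participants needed and 61 to enrol. It also says: "The type 1 error (alpha) was set at 0.05 and power was set at 80"%. The enrolment figure reproduces: 35/(1 − 0.42) = 60.3, rounded up to 61. The 35 can be neither reproduced nor refuted, because cluster size and variance components are not given. A plain one-sample formula gives ((1.960 + 0.842) × 0.47/0.55)² = 5.7. This matters here only because the article does not say what kind of SD 0.47 is. Three readings of the within-person residual SD, s, are carried as assumptions:

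- A: 0.47 is the SD of a change score, so s = 0.47/√2 = 0.332.
- B: 0.47 is itself the residual SD, so s = 0.47.
- C: s is back-solved so that 35 participants give 80% power for the step contrast, s = 1.006.

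**2. Bias from the schedule.** The baseline visits fall at weeks 0, 6 and 12 (mean 6), and T3 at 12 + 24 = 36. A steady weekly slope enters the step contrast multiplied by 36 − 6 = 30 weeks. Relative to the drift over the 12-week baseline, that is 30/12 = 2.5. No SD is needed.

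**3. Standard errors**, with participant intercepts, independent residuals and n participants:

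- Step contrast: s√(1 + 1/3)/√n = 1.155 s/√n.
- 12-week baseline drift: Sxx = 36 + 0 + 36 = 72, so 12s/√(72n) = 1.414 s/√n. With these three visits the fitted drift is simply T2 minus T0.

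**4. Check against false effect.** For a 12-week drift D, z(PRET)/z(check) = 2.5 × 1.414/1.155 = 3.06. The inverse is 0.327, and s and n cancel. Two-sided 0.05:

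| PRET falsely significant | z(PRET) | z(check) | Check detects |
|---|---|---|---|
| 50% | 1.96 | 0.64 | 10% |
| 80% | 2.80 | 0.92 | 15% |
| 90% | 3.24 | 1.06 | 18% |
| 95% | 3.60 | 1.18 | 22% |

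**5. Sensitivity of the 80% row.** With AR(1) residuals (6-week correlation 0 to 0.9), detection is 15% to 34%. With random slopes (SD of the 12-week drift 0 to 1 residual SD), it is 15% to 43%.

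**6. In HbA1c units.** A bias of half the planned effect (0.275) needs a baseline drift of 0.275/2.5 = 0.11. A bias equal to the whole effect (0.55) needs 0.22. Entries are for n = 35 / n = 61.

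| Reading | Half: PRET falsely significant | Half: detected | Full: detected |
|---|---|---|---|
| A | 99% / nearly 100% | 28% / 45% | 79% / 95% |
| B | 85% / 98% | 17% / 25% | 50% / 73% |
| C | 29% / 46% | 7% / 9% | 15% / 23% |

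A 20,000-run simulation under reading A with half-effect drift found PRET significant and the check passed in 72% (n = 35) and 56% (n = 61) of runs.

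**7. Price of adjusting for trend.** With a linear time term on T0 to T3, the variance multiplier becomes 1 + 1/3 + 30²/72 = 13.83 instead of 1.33. The standard error grows by √(13.83/1.333) = 3.22. Power for −0.55, before trainer clustering, is:

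| Reading | n = 35 | n = 61 |
|---|---|---|
| A | 75% | 94% |
| B | 46% | 69% |
| C | 14% | 21% |

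**8. A change that plateaus.** If a gain L appears between T0 and T1 and then holds (0, L, L, L), the step model is biased by L − 2L/3 = +0.33L. The fitted 12-week drift is L, so the trend-adjusted estimate is 0.33L − 2.5L = −2.17L. That is 6.5 times as large and in the opposite direction.

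**The case against.** The plan does recognise the stability assumption and looks at it for every outcome. The article does not expressly exclude a time term, and what happens after the check may be set out in a fuller plan. A reader might infer that a non-significant slope will be taken as proof of no slope. The text gives no such rule, and that reading is not relied on here. What stands is that the effect coding and the covariates are stated, and time is not among them.

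A reader might also infer that any drift whatever is counted as a PRET effect. That is too strong. Drift that runs through recorded sport or medication changes is adjusted for, and the factor 2.5 applies only to drift that stays linear to week 36. Learning on the fitness tests may well plateau, in which case step 8 shows that the planned model is only mildly biased and a linear correction does more harm.

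Nor is the check useless. On reading A it detects a drift as large as the whole planned effect 79% or 95% of the time. The percentages in step 4 are conditional on drifts chosen for illustration, since the article gives no expected drift.

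Finally, the Discussion justifies the single-group design and admits residual confounding from unmeasured care. That disclosure is fair, but it does not mention drift over time.

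**Conclusion.** The point holds in limited form and should be fixed. The factor of 2.5 follows from the visit schedule for any linear drift that the recorded covariates do not explain. The weakness of the check against drifts just large enough to produce a false PRET result (10% to 22% detection for false-positive rates of 50% to 95%) assumes linear drift and independent residuals. Under the alternatives tried, detection in the 80% case stays below one half. For a drift worth half the planned HbA1c effect, detection is 7% to 45% over all SD readings and both sample sizes. These figures are for the linear models; the logistic models were not worked out.

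The documents do not support the stronger conclusion that the trend-adjusted estimate should replace the step estimate or decide attribution alone. It extrapolates 24 weeks beyond a 12-week baseline, overcorrects a plateau, and does not remove changes that begin after week 12. No single power figure for it can be defended either, because the SD of 0.47 is undefined.

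**What to change.** Keep the step model as planned. For each primary outcome, before analysis:

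- Report the estimated 12-week baseline drift with its confidence interval, in place of reliance on its p-value.
- Pre-specify, as a sensitivity analysis, the T0 to T3 model with the PRET indicator plus linear time in weeks. In balanced data with independent residuals this equals the step estimate minus 2.5 times the 12-week drift, so it is one extra model.
- State how the two are read together. Where the step and trend-adjusted estimates disagree, or the drift interval does not exclude a drift that could explain the effect (the step estimate divided by 2.5; for −0.55, a drift of −0.22), describe the result as a pre-post change not separable from time trend.
- State the limits of the linear-trend estimate given in the verdict, and that it is not the sole deciding rule.

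The cost is plan wording and one model per primary outcome, with no new data or visits. The downside is a standard error about 3.2 times larger. Power for −0.55 is then 14% to 75% with 35 participants or 21% to 94% with 61, before trainer clustering, so some real effects will be reported only as pre-post change.
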